#### Sample size

For the purposes of our sample size calculation, the primary clinical outcome is the difference in mean HIT-6 score at 12 months post randomisation between the self-management group programme and the usual care relaxation therapy (control arm). The HIT-6 outcome measure is a continuous scale with higher values indicating more severe impact on daily life. From our systematic reviews, we anticipate a worthwhile difference to be 2.0, that is, mean outcome in the control arm is 2.0 units higher than for the intervention.^27 43^ In our feasibility study (n=114), the SD of the HIT-6 score at baseline was 6.87.^44^

Participants are randomised to either the self-management group or usual care and relaxation therapy. In this design, there may be a clustering effect in the self-management group and not in the control arm, which needs to be allowed for in the sample size calculation. Based on similar trials, we assume that the intraclass correlation coefficient is 0.01.^22^ The anticipated average size of the self-management programme is 10.

The minimum sample size required was estimated using Moerbeek and Wong’s method to account for grouping in one arm.^45^ To detect a between-group difference of 2.0 with SD of 6.9 (a standardised mean difference of 0.29) and assuming that the ratio of the total variance in the self-management group to the relaxation therapy is 1 at the two-sided 5% significance level and at least 90% power, the sample size required is 523 participants (253 in the relaxation group and 270 in the self-management group).

In the feasibility study, the overwhelming majority of those recruited, approximately 95%, chronic migraine; just 5% had chronic tension type headache. We want to be able to draw definite conclusions on the specific subgroup of chronic migraine. Therefore, we will base our sample size and primary clinical outcome on the population with chronic migraine. Therefore, based on 95% of our sampled population with chronic migraine and accounting for a 20% loss to follow-up as above, the sample size we would require is 689 with 333 to the relaxation arm and 356 to the self-management programme.

In the feasibility study, we recruited around 1/1000 of practice population to take part^44^; we therefore anticipate we need to recruit from around 100 general practices with a combined list size of around 700 000.

In consultation with the Data Monitoring and Ethics Committee (DMEC), we will review the sample size around halfway through recruitment to ensure we have recruited sufficient participants with chronic migraine and revise our estimates using within trial data on the variance of our primary outcome at baseline. This review will be based on the headache classification and actual baseline SD of our sampled population. We might also need to recruit some additional participants to ensure that the final group sessions at each site are adequately populated.

#### Recruitment

Participants are identified and invited into the study in two ways. First, practices run electronic searches on their databases to identify people who have consulted with headaches or have been prescribed migraine specific drugs (eg, triptans and pizotifen) in the preceding 2 years. Practices then screen the lists for those it would be inappropriate to approach (eg, poorly controlled serious mental illness, terminal illness or known secondary causes of headache such as primary or secondary brain tumours) and send approach letters to the remainder.

People can self-refer to the trial. Participating general practices, the principal pharmacies used by their patients, are supplied with a study poster for display in patient areas inviting people to contact the study team if they have headaches and are interested in participating. Information about the trial is made available on the poster (in general practices and pharmacies) and websites (https://warwick.ac.uk/fac/med/research/ctu/trials/other/chess/ and https://warwick.ac.uk/fac/med/research/ctu/trials/chess. People who find about the trial through the internet or following media exposure, and can travel to sessions, can also self-refer to the trial.

Using both approaches will allow people receiving GP treatment for chronic headaches who are not coded in the GP system as having headaches, and those who are self-medicating their headaches, the opportunity to join the study. We anticipate that we will primarily recruit people registered with participating practices; however, we will not restrict recruitment to those registered with participating practices.

In addition to these two main recruitment strategies, a study press release was submitted in January 2018, which was picked up by various media outlets and generated further interest in the study from potential participants.

The study coordinating team contact people expressing an interest in the study and check that they are eligible, explain the study and obtain participant’s verbal consent to start completing an electronic headache symptom severity, duration and frequency diary (or paper version where there is no access to the internet). The electronic diary is completed weekly for the first 6 months and subsequently monthly until the end of follow-up at 12 months. The electronic diary is used to identify any early effects of rebound headache in those with MOH. At this time participants are sent a baseline questionnaire and consent form to return in a freepost envelope.

Following receipt of baseline questionnaire and consent form, participants are contacted by phone for a nurse headache classification interview. People whose headache is confirmed to meet our entry criteria are then eligible for randomisation. If the nurse has a concern that the potential participant may have another headache type, there is a second interview with a doctor skilled in the management of headache disorders from the National Migraine Centre (http://www.nationalmigrainecentre.org.uk/). This is to ensure no one is inappropriately excluded and that people with a headache type needing more specific treatment are directed towards appropriate treatment. For example, 2/108 people in our feasibility study had cluster headaches.^44^ In such cases, we write to the GP and the participant with details on the excluded headache type and explain that they no longer fit the inclusion criteria for the CHESS trial.

### Assignment of interventions

#### Randomisation

The randomisation is stratified by geographical locality (Midlands and Greater London) and headache type (six possible headache types: chronic tension type headache, probable chronic migraine and definite chronic migraine with or without MOH) using minimisation. Randomisation takes place using an online application specifically developed for the CHESS Study by the Warwick Clinical Trials Unit (WCTU) programming team.

Randomisation takes place when there are around 20 participants who would be able to attend a local group if randomised to the active intervention. Typically these will come from 4 to 5 proximate general practices. However, people from other localities who are unable to attend a more local group and people who have self-referred to the study who are willing and able to travel to the sessions will also be included. By randomising in groups around 2 weeks prior to the start of a group, we are able to minimise any delay between randomisation and start of the intervention and ensure everyone has adequate follow-up from when they might have been exposed to the intervention. For those that are subsequently unable to attend after randomisation to a group, we will offer them another group where possible.

#### Allocation concealment and protection from bias

Allocation concealment will be maintained by using Warwick CTU’s centralised randomisation service. All baseline data will be collected prior to randomisation. Blinding will be impossible for participants, facilitators and the central co-ordinating CHESS team. All data entry and checking is done blind to treatment allocation. The unbalanced randomisation means it is not possible blind the trial statistician to treatment allocation.

Our primary outcome is a participant completed outcome. Inevitably, participants will be aware of their treatment allocation. We will develop and sign off a detailed prespecified statistical analysis plan before allocation codes are released.

### Data collection, management and analysis

#### Data collection methods

Data will be collected using two methods: postal survey questionnaires and a smartphone application (App) for headaches. All participants will be asked to complete a smartphone app about their headaches. If they do not have access to a smartphone or do not wish to use the app, a paper copy will be provided. Participants will initially complete the app weekly for up to 6 months to cover any period of withdrawal from medication, then monthly thereafter (still requiring them to reflect over the previous 7 days) until the end of the study at 12 months after randomisation. We are working with Clinvivo Ltd, a University of Warwick spin-out company specialising in electronic data collection, to capture data on headache frequency, duration and severity electronically using a smartphone app (table 3 shows the questions completed by participants and mode of response required). The data from the questions in the electronic diary will be numerical and downloaded into a WCTU database using a randomly generated 256-bit Advanced Encryption Standard (AES) key. At the end of the participants’ 12 months, they will be provided with a summary report of their headache application data.

**Table 3 T3:** Questions completed on the smartphone app

Question	Mode of response
On how many of the last 7 days have you had a headache?	Insert number of headache days
On those days you had a headache, on average how long did they last?	Insert number of hours
On those days you had a headache, on average how severe were they?	Scale of 0–10 (with 0 being no pain and 10 extremely severe pain)

Reminders are sent to those participants who fail to downloaded the app or have not responded for more than 3 weeks. Reminders are sent by email or by post if there is no email address given.

A daily detailed paper headache diary is kept only by the intervention arm participants, and the data will not be analysed by the study team but kept as a record by the participants and used during the one to one consultation where it will be collected and kept by the research team.

#### Data management

All questionnaire data received by the trial team are reviewed for completeness and entered onto a secure, backed-up bespoke database held at WCTU, which will be accessible only by authorised members of the team. Data from the smartphone app are downloaded securely (as described above) into the trial database. All data are checked when received, and any queries relating to the HIT6 CHQLQ or EQ5D are raised with the participant by telephone.

#### Statistical analysis of effectiveness and harms

Our primary endpoint analyses will be based on the 12-month data.

Participants’ characteristics and reported outcomes will be summarised as means and SDs (for continuous data) or frequencies and percentages (for categorical data) by treatment arms. Difference between baseline and the three follow-up time points (4, 8 and 12 months post randomisation) will be computed for the primary and secondary outcomes by treatment arms.

The primary analysis approach will be intention to treat; that is, the data will be analysed according to the treatment the participant was originally allocated to, irrespective of what they actually received. We will explore the possibility of carrying out a complier averaged causal effect analysis as a sensitivity analysis. Our primary analysis will be the difference between the self-management therapy (intervention) and the relaxation therapy (control) groups with a 95% CI in the population with chronic migraine – if the proportion of participants with chronic tension type headache is ≤15%. The hypothesis testing of the primary outcome will be two sided at the 5% level, and the main analysis will estimate the treatment effect using a multilevel model to account for clustering (the model used to design this main trial). We will also present results for the whole population (all headache types). If the proportion of chronic tension type headache is >15%, then the primary analysis will be according to the whole population of chronic headache (chronic migraine and tension type headache). Our experience is that NICE was specifically interested in data on specific headache types, excluding data that reported mixed population of people with chronic headaches. We will, therefore, in addition to our primary analyses, present the results (mean difference and 95% CI) for each of the two headache types with or without MOH separately and present results for those with or without medication overuse separately to facilitate future meta-analyses and inform future condition specific guidelines. All analyses will be adjusted for the randomisation stratification factors (types of headache and geographical locality), sex, age and the baseline value of the dependent variable.

Similar analyses will be performed for all the other secondary outcomes. Prespecified subgroup analyses using formal statistical tests for interaction will examine whether baseline anxiety, depression and severity are moderators of treatment effect.^46^ We will assess the level of missingness in the primary outcome, and if required, we will use appropriate multiple imputation techniques to impute data and estimate the treatment effect as a form of sensitivity analysis. A full statistical analysis plan, including all primary and secondary analyses, will be written and signed off prior to releasing allocation codes to analysts and others involved in developing the plan.

Using the data from the smartphone app, we will generate a composite score for headache impact over the 1 year of follow-up as the function of headaches days × average duration × average severity. Presenting these data graphically will allow any early benefits or harms from the intervention to be identified.

#### Health economic evaluation

Our economic evaluation will be conducted alongside the trial, and we will initially adopt a 1 year time horizon from both an NHS and personal social services perspective and, separately for the purpose of a sensitivity analysis a broader societal perspective, to estimate the cost-utility of the intervention. Resource use data will be collected to explore the costs of the delivery of the intervention and to estimate the key cost drivers. This will mainly consist of visits to the GP practice, medication usage and any adverse events (AEs) or length of stay in the hospital. In terms of costs to society, we will estimate time off work and any productivity losses associated with chronic headaches. Resource use information will be collected using self-completed postal questionnaires completed at 4, 8 and 12 months after randomisation, as well as the use of routine health service data collected from general practice records. Resource input will be valued using national estimates of unit costs such as the Prescription Cost Analysis database or the Unit Costs of Health and Social Care compendium.^47^ Preference-based health-related quality of life outcomes will primarily be assessed through the completion of the EQ-5D-5L at each follow-up point.^48^ Quality-adjusted life-years (QALYs) will be calculated as the area under the baseline-adjusted utility curve and will be calculated using linear interpolation between baseline and follow-up utility scores.

The results of the economic evaluation will be presented using incremental cost-effectiveness ratios, expressed in terms of incremental cost per QALY gained, and cost-effectiveness acceptability curves generated via non-parametric bootstrapping.

More extensive economic modelling using decision analytic methods will extend the target population, the time horizon to 5 years as the long-term natural history is unclear and the decision context, drawing on best available information from the literature together with stakeholder consultations to supplement the trial data. Longer term costs and consequences will be discounted to present values using nationally recommended discount rates recommended for health technology appraisal. We will use probabilistic sensitivity analysis to estimate the impact of uncertainty over model parameters. We will also use simple sensitivity analysis to assess the robustness of the results to changes in deterministic parameters such as medication dosages, costs, discount rate and time horizon for patients presenting with chronic headaches. We will also explore cost-effectiveness of the intervention by conducting subgroup analyses for the different headache types.

### Monitoring, ethics and dissemination

#### Programme steering committee (PSC)

We have established a PSC to oversee the whole programme of work. The PSC functions specifically as a trial steering committee specifically for this trial. The PSC consists of seven members including two patient representative. The PSC will be responsible for oversight and monitoring and will consider any information from surveillance activity of other research in the field.

#### Data monitoring and ethics committee

A DMEC has been convened consisting of an independent statistician, a triallist, a clinician and a lay member. Confidential reports that summarise the trial data and safety data will be reviewed by the Data Monitoring Committee (DMC). The DMC will advise the PSC as to whether to continue, amend or terminate the trial based primarily on safety and efficacy considerations

#### Harms/AEs

An AE or serious AE is any event that takes place on the way to, during or on the way home from the intervention course. This includes the 2 days of the group course and the one-to-one nurse appointment. Our experience across multiple studies of group interventions is that AEs that are directly attributable to the intervention are rare.

Events during the session, such as severe psychological disturbance, any mild or moderate levels of emotional distress as a result of discussing experiences of living with chronic headache, a fall during travel to and from the venue or any other AEs, occurring during the delivery of the intervention will be reported to the trial co-coordinator by the intervention team. Any short-term increase in headaches as a consequence of medication withdrawal will be captured using the smartphone app (or paper version for those without access to a smartphone).

All AEs will be managed in line with Warwick CTU’s standard operating procedures.

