The sessions take place on weekdays and, where possible, during school hours to accommodate those with child care responsibilities. Sessions are held in easily accessible community venues and GP practices.

Participants in the intervention arm are asked to complete a paper headache diary for a period of up to 8 weeks prior to the 2-day programme. A one-to-one, individually tailored nurse-led consultation follows the 2-day programme. During this session, the nurse classifies the participant’s headache type, discuss medication and lifestyle factors and explore participants’ goals. This discussion is backed up by written information (for patient and GP), consistent with NICE guidance, to support shared informed decision making between the patient and their GP, about medication choices.^25^ All participants will be offered telephone follow-up for up to 8 weeks. The frequency of these follow-up calls will be individually negotiated and agreed with participants during the one-to-one consultation. Full details of the intervention content have been published elsewhere.^23^

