#### Control intervention

Previous studies of this nature have reported that a usual care control arm was not an incentive to join the study.^15^ We know from experience that patients enjoy the relaxation part of pain self-management programmes.^17^ Therefore, as an incentive to participate, the control group receive standard usual care plus a relaxation CD and instructions for use over the duration of the study, up until final follow-up at 12 months. Participants are free to continue using the relaxation CD thereafter should they wish.

As all participants in the trial have a headache classification interview prior to randomisation, we feed back the results of that classification interview to control participants, and their GPs, together with advice on headache management. In this way, we ensure all participants receive best usual care.

The relaxation CD or downloadable MPG file (from the CHESS website) consists of a 17 min relaxation audio script that starts by focusing on the breath before talking the participant through progressive relaxation of muscles. The participants in the control group choose when, where and how often they do the relaxation but are advised to try it two to three times a week or as often as they feel appropriate over the course of the study.

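### Adverse events can be recorded only at or around intervention sessions, so AE and SAE rates have no comparator, and later harms other than headache or scale changes have no stated AE route

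*Protocol article*

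**What the plan says.** The Harms/AEs section of the protocol article fixes what counts: "An AE or serious AE is any event that takes place on the way to, during or on the way home from the intervention course". It adds: "This includes the 2 days of the group course and the one-to-one nurse appointment". Reporting follows the same boundary, since events "occurring during the delivery of the intervention will be reported to the trial co-coordinator by the intervention team". The section sends one later harm elsewhere: a temporary rise in headaches after medication withdrawal is to be picked up by the smartphone app or its paper version.

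Under Control intervention, "the control group receive standard usual care plus a relaxation CD and instructions for use over the duration of the study". Controls and their GPs also receive the result of the classification interview with advice on managing headache. No session or appointment is described for them.

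Under Interventions, the nurse consultation comes after the group course. It covers medication and is backed by written information for patient and GP "to support shared informed decision making between the patient and their GP, about medication choices". Within that description of the active arm, "All participants will be offered telephone follow-up for up to 8 weeks".

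Two other sections depend on safety information. Data monitoring and ethics committee says: "The DMC will advise the PSC as to whether to continue, amend or terminate the trial based primarily on safety and efficacy considerations". Health economic evaluation says of resource-use data: "This will mainly consist of visits to the GP practice, medication usage and any adverse events (AEs) or length of stay in the hospital". The sources it names are postal questionnaires at 4, 8 and 12 months and routine general practice records.

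**The concern.** An event is an AE or SAE only if it is tied to attending something that one arm alone attends. A control participant admitted to hospital during follow-up has no SAE under this rule. Nor has an intervention participant admitted three weeks after the nurse appointment. AE and SAE figures reported by arm would show some number against a zero that the definition has produced.

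The window also fits this intervention poorly. One way the programme may act is through decisions on medication taken with the GP after the consultation, with telephone support continuing for weeks. A side effect of changed medication, or a serious event in that period, would come after the window has closed. Because controls and their GPs also receive headache advice, medication may change in both arms, and a record kept in one arm cannot show a difference in either direction.

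Finally, the term AE appears in the economic section with a reach of 12 months. A reader cannot tell which events are to be costed.

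**Working it through.** No figure in the article depends on the AE definition, so there is nothing of the plan's own to reproduce on this point. The check is to set the sections side by side and then size the window.

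**Who can have an AE?** Harms/AEs requires travel to or from, or attendance at, the group course or the nurse appointment. Control intervention describes a relaxation recording used when and where the participant chooses, plus usual care and written feedback. No control participant can meet the definition.

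**When can an AE occur?**
- Inputs: 2 course days and 1 consultation (Harms/AEs); 12 months of follow-up, taken as 365 days.
- Per intervention participant: (2 + 1) / 365 = 3 / 365 = 0.8%. This assumes that the consultation is on a separate day, which the article does not say. If it shared a day with the course, the share would be 2 / 365 = 0.5%.
- Per control participant: 0 / 365 = 0%.
- Whole trial at the planned sizes (356 intervention, 333 control): 3 × 356 = 1,068 person-days out of (356 + 333) × 365 = 251,485, or 0.4%.
- Telephone support outside the window: up to 8 × 7 = 56 days, or 56 / 365 = 15% of follow-up.

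**What else captures harm, and in which arms?**

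| Source | Arms | Period | What it can show |
|---|---|---|---|
| Session AE record (Harms/AEs) | Intervention only | Travel and session time | Any event |
| App or paper version (Data collection methods, Table 3) | Both | Every week for 6 months, then every month to 12 months | Headache days, duration, severity |
| HADS, SF-12, EQ-5D-5L, HIT-6, Troublesomeness Grid (secondary outcomes, Table 2) | Both | 4, 8 and 12 months | Distress, quality of life, headache impact, bodily pain |
| Resource use (Health economic evaluation) | Not restricted to one arm | Questionnaires at 4, 8 and 12 months, plus GP records | GP visits, medication, hospital stay |

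The gap is therefore specific. The app's three questions concern headache alone, and the scales measure symptoms and function. A drug side effect, an admission or another serious event weeks after the course is none of these. Such an event might leave a trace in the resource-use data, but the article does not direct those data into a comparison of safety.

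**Is the term used consistently?** Under Harms/AEs an AE is a session event noted by the delivery team. Under Health economic evaluation it is an item of resource use obtained from participants and GP records over 12 months. The two meanings differ.

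**The case against.** The strongest reply is that the trial does assess harm in both arms, and this is largely right. The article expects rebound headache and assigns it to the app, which everyone is asked to complete. The section on Statistical analysis of effectiveness and harms says that plots of the app composite will be used to look for early harm as well as benefit. Distress and bodily pain are measured in both arms by validated instruments. A reader might infer that harms cannot be compared at all, or that no harm from medication change is counted. The documents do not support either reading.

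Two further inferences go too far. One is that AE costs will fall on the intervention arm alone. The economic section names questionnaires and GP records as its sources, not the session record, so the defect there is a mismatch of terms. The other is that the DMC will be unable to see an excess of serious events. Its reports are said to cover both trial data and safety data, and their content is not shown.

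The article also gives a reason for its choice: in the team's experience, events directly attributable to such group interventions are rare. It refers the management of AEs to the trials unit's standard operating procedures, which are not shown. Neither fully answers the point. Rarity of attributable events does not help when attribution has to be judged without a comparator. The procedures may govern handling, but the article itself states what an AE is, and that statement excludes the control arm.

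**Conclusion.** The point holds in a limited form. As defined, AE and SAE recording covers travel and session time in the intervention arm only. That is about 0.8% of each intervention participant's follow-up, on the assumption of a separate day for the nurse appointment, and none of any control participant's. AE and SAE rates therefore cannot be compared between arms. Later harms other than headache worsening or changes on the patient-reported scales have no stated AE route, although the intervention supports medication decisions and continues by telephone for up to 8 weeks. The use of AE in the economic section does not match the definition under Harms/AEs, and the two must be reconciled.

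The point does not bear on the primary analysis or the sample size. It rests on the article's wording; the full protocol, the standard operating procedures and the DMC reports may hold more. It is a cheap improvement rather than a flaw that threatens the trial's conclusions.

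**What to change.** 1. Keep the present record, call it an intervention-session safety log, and state that its counts are not comparable by arm.
2. Add a table by arm of hospital admissions and length of stay over 12 months, drawn from the 4-, 8- and 12-month questionnaires and the GP records already planned. Add deaths and emergency attendances only if GP or withdrawal records hold them. The economic section lists neither, so their availability is an assumption to be checked first.
3. Provide that table to the DMC alongside the session log.
4. In the Health economic evaluation section, state that AE costs come from this two-arm source, and align the term with the Harms/AEs section.

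The cost is some wording and a little extra tabulation, with no new data collection. The article reports that recruitment had finished and follow-up was under way in August 2019, and the added table needs only data that were due to be collected in any case. The downside is reliance on self-report and routine records, which will be incomplete and, for self-report, come from participants who know their allocation.
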